### Intervention Overview

The ART-C intervention consists of a bundle of digital health-supported services and traditional care coordination activities that can be used outside of the research context. When a clinic begins implementation of ART-C, all clients at the clinic immediately have the opportunity to download the Connections app and use its standard features without sharing any individual-level data with researchers. This is referred to as patient-directed engagement with the app. Individuals who use the Connections app at this level can participate in discussion forums and view resource pages alongside clients receiving services at more than 250 recovery- and prevention-oriented organizations across the United States who subscribe to the Connections app. Patients using the Connections app at this level are not considered to be research participants.

In addition to the standard level of app engagement open to all Vivent Health clients, patients with risk factors for poor engagement in care are invited to access more intensive and personalized features of ART-C as part of a research protocol. These risk factors are described in the formal participant eligibility criteria and capture a patient’s HIV visit attendance history, viral load values, and self-report substance use history. Patients meeting eligibility criteria have access to additional app features and the opportunity to interact with specially trained staff who monitor activity within the Connections app and interact with study participants on a study-specific discussion board. This is referred to as the clinic-supported intervention engagement. These 2 levels of intervention engagement allow the most resource-intensive components of the intervention to be targeted toward patients at greatest risk for viral nonsuppression, while offering all patients the opportunity to participate in the online community fostered by the Connections app.

### Patient-Directed Intervention Components

#### Peer Mentors

Peer-based support is an evidence-based strategy for supporting care engagement [39-41]. It also reduces racial and ethnic disparities in health care by addressing stigma and discrimination [42-44]. Upon implementing ART-C, Vivent Health recruited and trained 6 peer mentors living with HIV who demonstrated resilience in meeting HIV treatment goals and overcoming the effects of discrimination, addiction, or other life challenges. Candidates were identified by soliciting nominations from Vivent Health case managers and health care providers who had been oriented to the goals of the intervention. Peer mentors receive a monthly stipend (US $100) to cover phone and data services and as a token of appreciation for the valuable service they provide. Recruitment and training of peer mentors occur before the intervention starts in each clinic, using modified curricula developed for use by the HRSA-funded AIDS Education and Training Centers.

#### The Connections App

Developed and marketed by CHESS Health, the Connections app offers users anytime and anywhere access to a suite of digital health services, including an online community forum used by people engaged in SUD services across the United States. The recovery-oriented community forum is monitored and moderated by a peer engagement team employed by CHESS Health, consisting of trained peer support specialists who can provide feedback and support to people with SUDs. For the ART-C intervention, the research team worked with CHESS Health to build and deploy a parallel HIV care-oriented community forum, which is moderated by Vivent Health peer mentors and allows for online discussion of topics relevant to patients with and without SUDs, including medication adherence, stigma, and other challenges encountered by people living with HIV. Furthermore, the Connections app contains gamification features, where users can earn points for active engagement in the online community and for extended periods of abstinence from drugs or alcohol. The app also supports private discussions among a smaller number of users in group chats, as well as personal messages between users or between users and staff.

### Clinic-Supported Intervention Components

While the Connections app is available to the full clinic population, more intensive support involving digital health–enhanced, person-centered care coordination can only be delivered to a subset of patients due to staffing and other resource limitations. To maximize the potential impact of the ART-C intervention, the research team consulted with Vivent Health leadership to develop the eligibility criteria provided in Textbox 1 for the clinic-supported arm of the intervention.

Our target study population involves people at risk of viral nonsuppression and lapses in HIV care due to current or past substance use and history of disruptions to HIV care engagement or viral suppression, which align with these criteria.

Inclusion and exclusion criteria.
**Inclusion criteria**
Aged 18 years or moreCan read and write in EnglishReceiving medical care for HIV treatment at Vivent Health (confirmed by electronic health record review)At least 1 of the following requirements must be met based on self-report: have a self-reported lapse in medication, which is defined as missing 2 or more doses of medication within a 1-month period; have missed at least 1 appointment while receiving medical care at a Vivent Health clinic; have a history of, or current, substance use disorder, or a report that substance use has caused problems for them at some point in their life
**Exclusion criteria**
Not currently having a smartphone and unwilling to obtain a smartphoneAppearing to lack the capacity to consent, as evidenced by an inability to read, write, speak, or otherwise provide informed consent due to acute intoxication or chronic conditions

### Research Care Coordinators

Two new staff members with prior employment experience in HIV medical case management were hired by Vivent Health to be fully dedicated to the ART-C intervention. The research care coordinators have a hybrid role on the Vivent Health care team: they function as research specialists, recruiting, screening, and obtaining informed consent for participants in the clinic-supported intervention, and serve as liaisons between patients who engage with app services and other health care professionals on the patients’ care team. Research care coordinators are credentialed as Vivent Health case managers; have access to patients’ medical records; and, with patient consent, can communicate with medical health care providers, case managers, and other staff about or on behalf of patients enrolled in the ART-C intervention.

### Weekly Check-In Surveys and Red Flag Alerts

Patients enrolled in the clinic-supported intervention are sent a weekly check-in survey via the Connections app that assesses common barriers to care, medication adherence, and drug or alcohol use. The content of the weekly survey was developed and pilot-tested in previous research to provide a near real-time indication of patient experiences that may signal an increased risk of lapses in care [29]. While clients are able to reflect on and report notable barriers from the previous week, the results of these surveys will not be automatically shared with their care team. At the end of the survey, clients are required to opt in or out of having their responses forwarded to their care team for triage. Selecting to opt in means that the clinical research coordinator and care team will adhere to a predetermined escalation procedure for assisting the client with their disclosed barriers.

### Participant Recruitment

On a quarterly basis, the Vivent Health data analytics group will send a list of all patients receiving HIV medical care to the ART-C study team. The list will be used to recruit for the clinic-supported intervention of the study. Patients are contacted through mass messaging campaigns using the MyChart feature of the Epic EHR system, a secure text messaging platform (Artera); direct messaging through MyChart; or direct messaging through the preferred contact method listed in their EHR. For patient privacy, patients who receive messages through mass messaging campaigns will receive a link only to the Connections app download page. Patients who receive direct messaging through MyChart or via their preferred contact method will receive a link to the eligibility survey and app download page. To participate in the study, patients must also have a smartphone and be willing to download the Connections app, which will prompt them to complete a brief questionnaire to assess eligibility for the clinic-supported intervention. Eligible patients will receive a follow-up message asking them to schedule a phone or video appointment with a research care coordinator to review the informed consent document and receive a brief orientation to the ART-C intervention and the Connections app. Patients who do not meet the eligibility criteria will receive a follow-up message informing them that they are not eligible to participate in the clinic-supported arm of the study, but they are encouraged to use the Connections app. People who download the app but do not complete the eligibility screener will receive an additional message reminding them about the opportunity to screen for eligibility for the clinic-supported intervention.

For each of the 8 Vivent Health sites, eligibility assessment and screening will continue until the accrual target is reached or until the end of the 1-year implementation period, whichever occurs first. Participants who enroll but later withdraw or are lost to follow-up will not be replaced by newly enrolled participants.

### Data Collection

We will use the RE-AIM model to guide our overall evaluation of implementation. RE-AIM is a comprehensive framework that assesses 5 dimensions: reach, effectiveness, adoption, implementation, and maintenance [45].

The primary “reach” measure will be the percentage of Vivent Health patients with HIV who have downloaded and used ART-C, along with their sex, racial, and ethnic characteristics. The primary “effectiveness” outcomes (missed HIV care visits and viral nonsuppression) will be evaluated from clinical EHR data documenting HIV viral load results and the status (attended and missed) of scheduled HIV care visits. We will also describe Connections app use and collect quarterly surveys from patients in the clinic-supported intervention. “Adoption” at the patient level is based on research-driven metrics of meaningful use for mHealth, defined as a patient accessing any part of ART-C beyond the home page during a given week in the 12-month period after downloading the app [46].

“Implementation” will be evaluated based on fidelity to key components of ART-C at the clinic level, using quantitative and qualitative methods. We will define fidelity in two dimensions: (1) the amount of the intervention received (ie, use of the dashboard) and (2) the quality of intervention delivery (ie, the intervention participant’s reflections on their experience using the dashboard and the effect it had on their approach to care delivery). “Maintenance” will be defined as follow-up on the effectiveness measures (viral load and missing visit rates) in the 6-month postintervention period.

Using qualitative interviews, we aim to gain rich insights into implementation and adoption processes at various sites from a diverse set of stakeholders involved in implementation. Data will be coded, and the analysis will help us refine the Connections app for future dissemination by determining individual and organizational conditions necessary to promote effectiveness. Interviews will be conducted with multilevel stakeholders, including study participants (10 to 20 interviews), clinic staff identified as change leaders (5 to 10 interviews), and the peer mentors (5 interviews).

### Analytic Strategy: Effectiveness and Maintenance

In the stepped-wedge design, each site functions as its own control or usual care group before the implementation of ART-C. During this period, clinics treat patients with HIV using existing, standard treatment protocols and do not yet have access to the Connections app. To characterize intervention effectiveness, we will model site, time, and intervention status as predictors of primary outcomes using a repeated measures model to control for clustering by individuals and sites [47]. An indicator variable for intervention status will be modeled as 0 before intervention and 1 after ART-C is rolled out at each site. Random effects will be used to model the correlation between individuals within the same cluster (ie, site) in the stepped-wedge design. For a design with 8 clusters, 5 time points, and N individuals sampled per cluster per time interval, Y_ijk_ will be the response corresponding to individual k at time j from cluster i (i in 1,..., 7; j in 1,..., 8; k in 1,..., N) and Y_ij_ will be mean for cluster i at time j:

Y_ij_ = µ+ α_i_ + β_j_ + X_ij_θ

In this equation, α_i_ is a random effect for cluster i, β_j_ is a fixed effect corresponding to time interval j, X_ij_ is an indicator of the treatment status in cluster i at time j (1=intervention; 0=control), and θ is the treatment effect. The individual-level responses of no-show rates and viral suppression are binary, so the cluster-level responses Y_ij_ are proportions with variance σ_ij_^2^_e_ = µ_ij_ * (1 – µ_ij_). A variance inflation factor of 1 + (N – 1) ρ is incorporated into the analysis, where ρ is the intraclass correlation coefficient between individuals within the same cluster. Logistic generalized estimating equation (GEE) models will be determined using R statistical software (version 4.3.3; R Foundation for Statistical Computing) with geeglm (family=binomial) [48].

After establishing the base model, we will include potentially confounding and moderating factors by adding covariates, interaction terms, and weighting methods to the models. Potential clinic-level confounders will include the racial and ethnic categories, gender, age, and diagnosis of a SUD.

Power and sample size calculations will be based on the study by Hemming and Taljaard [49]. For a stepped-wedge design with 8 clusters stepped in 1 to 2 clusters at a time over 5 time periods and an assumed intraclass correlation coefficient of ρ=0.10, the design effect relative to an individual-based randomized controlled trial is 3.0. Preliminary data suggest the percentage of enrolled patients with nonsuppressed viral load (HIV RNA ≥200) before intervention to be 26.7%. On the basis of consultation with clinic leadership and pilot data from a single site, we assume a meaningful effect size to be a 10 percentage point reduction in nonsuppressed HIV RNA tests in the study sites after intervention, to 16.7%. The 8 clinical sites average 526 active patients per site per year for an estimated total of 4208 potential patients. We aim to reach approximately 15% of clinic patients using patient engagement strategies geared toward helping those patients most likely to benefit from the clinic-supported intervention. We hypothesize that the implementation strategy can effectively reach 631 (15%) patients and achieve a 68% improvement in viral load suppression among this highly vulnerable population. On the basis of these assumptions, with 3682 active patients, our power to detect a 10 percentage point reduction in nonsuppressed viral loads will be 98.5% (1–β=.985). The study will be sufficiently powered (>80%) to detect up to a 7 percentage point reduction in patients with nonsuppressed viral load.

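### The primary model is described as random-effects but named as a logistic GEE, with the clustering level left open; clustered on 8 clinics with an uncorrected sandwich and z test, it would reject a true null in roughly 11-23% of trials

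*Protocol article*

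**What the plan says.** All of this is in the protocol article, Analytic Strategy: Effectiveness and Maintenance.

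- Predictors: "we will model site, time, and intervention status as predictors of primary outcomes".
- Dependence: "using a repeated measures model to control for clustering by individuals and sites".
- Clinic effect: "Random effects will be used to model the correlation between individuals within the same cluster (ie, site) in the stepped-wedge design". In the displayed equation the cluster term is a random effect, time is a fixed effect, and there is no clinic-by-period term.
- Estimator: "Logistic generalized estimating equation (GEE) models will be determined using R statistical software". The function is geeglm with a binomial family. No working correlation, cluster identifier, small-sample correction or reference distribution is given.
- Design: "For a design with 8 clusters, 5 time points, and N individuals sampled per cluster per time interval". The power paragraph has "8 clusters stepped in 1 to 2 clusters at a time over 5 time periods", and Table 3 shows four pairs of clinics. The index ranges printed with the equation (7 clusters, 8 times) do not match; 8 clinics and 5 periods are used below.
- Adjustment, after the base model: "Potential clinic-level confounders will include the racial and ethnic categories, gender, age, and diagnosis of a SUD". Interaction terms and weighting may also be added.

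**The concern.** The section describes more than one model. A random clinic effect, site as a fixed predictor and a GEE are different analyses. Clustering by individuals and by sites are also different choices of independent unit. An analyst could follow the text faithfully and arrive at tests with very different error rates.

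The named estimator is also delicate here. The GEE sandwich variance relies on many independent clusters. With 8 clinics, two per step and sizes from 170 to 1480, it tends to be too small. Both primary effectiveness outcomes, missed visits and viral nonsuppression, go through this analysis. A nominally significant result could therefore reflect understated standard errors.

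**Working it through.** **1. The plan's own figure.** Inputs from the power paragraph: 26.7% versus 16.7%, 3682 patients, design effect 3.0, ICC 0.10. Alpha is not stated; two-sided 0.05 is assumed.

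- Effective n per arm = 3682 / 3.0 / 2 = 614.
- SE = √[(0.267×0.733 + 0.167×0.833)/614] = 0.0234.
- Power = Φ(0.100/0.0234 − 1.96) = Φ(2.32), about 99%, against 98.5% stated.
- For 7 points (19.7%): SE = 0.0240 and power about 83%, against more than 80% stated.
- The stepped-wedge design-effect formula with 4 steps and ICC 0.10 gives 2.93-2.99 on the total-observations scale for 50-526 patients per clinic-period, so 3.0 also reproduces.

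The power arithmetic is not the fault.

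**2. Parameter count.**

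| Model | Parameters |
|---|---|
| Base: intercept + 4 periods + treatment | 6 |
| Base + 7 site indicators | 13 |
| Base + one column each for race, ethnicity, gender, age, SUD | 11 |
| Base + Table 1 categories (race 4, ethnicity 1, gender 2, age 1, SUD 1) | 15 |

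The middle matrix of the clinic-level sandwich is a sum of 8 outer products whose scores add to zero, so its rank is at most 7. Any model with more than 7 parameters has a singular robust covariance matrix, whether covariates are measured on clinics or on patients. Software may still return a standard error for treatment.

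**3. Type I error, clustering on clinics.** Simulated trials with no effect: 8 clinics, 5 periods, 2 clinics per step, base rate 26.7%. Clinic variance on the logit scale = ICC/[0.267×0.733], with ICC 0.01-0.10. Cluster autocorrelation is 1.0 (no clinic-by-period variation) or 0.8. Cell sizes are equal (105 or 263 per clinic-period) or Table 1 sizes divided by 5. Each scenario has 1500 trials, so Monte Carlo error is about ±2 points.

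| Test (nominal 5%) | Equal clinics | Table 1 sizes |
|---|---|---|
| Uncorrected sandwich, z, exchangeable | 11-16% | 16-23% |
| Uncorrected sandwich, z, independence | 15-19% | 20-29% |
| Kauermann-Carroll-type, t(6) | 3-7% | 5-10% |

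Across scenarios, Mancl-DeRouen with t(6) gave 2-5%. Changing only the reference to t(6), with the sandwich uncorrected, gave 6-19%.

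**4. Type I error, other readings.** ICC 0.05, independence working correlation, uncorrected z test.

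| Model | Autocorrelation 1.0 | 0.95 | 0.8 |
|---|---|---|---|
| Site fixed, patients as clusters: equal / Table 1 | 5.5% / 4.4% | 8.5% / 13.3% | 17.1% / 27.1% |
| Site fixed, clinics as clusters: equal / Table 1 | 13.9% / 15.7% | 13.6% / 18.3% | 12.0% / 22.4% |
| Five clinic-level covariates, clinics as clusters: equal / Table 1 | 29.1% / 26.7% | 29.7% / 27.5% | 25.1% / 24.7% |

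The first row treats patients as independent observations.

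**5. Power of the corrected test.** 26.7% to 16.7%, ICC 0.10, 3682/40 = 92 per clinic-period, exchangeable, 600 trials (about ±3 points at 83%).

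| Test | Autocorrelation 1.0 | 0.8 |
|---|---|---|
| Uncorrected z | 98.7% | 79% |
| Kauermann-Carroll-type, t(6) | 90% | 57% |
| Mancl-DeRouen, t(6) | 83% | 46% |

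With ICC 0.02, Mancl-DeRouen power is 88% and 84%.

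**The case against.** **The missing correction belongs in the SAP.** The article never says uncorrected sandwich or z test, and naming geeglm does not by itself fix the variance estimator. This stands: silence on a correction is not the fault, and the error rates are conditional on that reading. It does not remove the contradictions in the text. The article names the estimator and function, and still leaves it unclear whether the model has a random clinic effect, a fixed one or neither, and which unit is independent.

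**One literal reading holds 5%.** With site as a fixed predictor and patients as clusters, error is nominal under the article's own equation, which has no clinic-by-period term. That is correct as far as it goes. It requires every clinic's underlying rate to follow the same time course apart from the intervention. The autocorrelations of 0.95 and 0.8 are assumptions, but even the milder one gives 9-13%.

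**Stronger readings the documents do not support:**

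- A reader might infer that the trial will have a false-positive rate of about 20%. The working correlation, patients per period and clinic-by-period variation are not stated, so only a scenario range can be given.
- A reader might infer that the primary model has more parameters than clusters. The base model has 6; covariates come after it and are called potential. The excess arises only if all are entered together, or if site enters as indicators.
- A reader might infer that moving covariates to patient level cures this. It does not, because 8 clusters set the rank limit.

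**Conclusion.** The concern holds in conditional form. The description of the primary analysis contradicts itself on random effects versus GEE and on the role of site, and it does not identify the GEE clusters. If clinics are the clusters and inference is the uncorrected sandwich with z, the type I error is about 11-16% with equal clinics and 16-23% with Table 1 sizes under exchangeable correlation, and higher under independence. Patient-level clustering with fixed sites is not a safe alternative, because it is valid only without clinic-by-period variation. These rates rest on two-sided 0.05, a base rate of 26.7% and the assumed cell sizes and correlations. The stated 98.5% power reproduces as arithmetic, but it does not describe a test that controls error with 8 clinics.

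**What to change.** - Name one primary model: logistic GEE with period and intervention, clustered by clinic. State the working correlation.
- Use a Mancl-DeRouen bias-corrected variance with a t reference on 8 − 2 = 6 df. The Kauermann-Carroll-type correction reached up to 10% with the unequal clinic sizes, so it is the less safe choice.
- As an alternative, use a permutation test that follows the randomization actually carried out. Individual randomization of clinics, two per step, gives 8!/(2!)⁴ = 2520 allocations. Randomization of fixed pairs gives 4! = 24, with a smallest attainable p of 1/24 = 4.2%. The article does not say which was used.
- Remove either the random-effects wording or the GEE wording, and state whether site is a predictor.
- Keep covariate-adjusted models secondary and small. Base terms plus all listed covariates (at least 11), or plus site indicators (13), exceed what 8 clusters support.
- Restate power for the corrected test.

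The change needs only text and code, and data collection runs to 2027, so it can be made before outcome analysis. The cost is real: wider intervals, a somewhat conservative test (2-5%), and power of about 83% instead of 98.5% at ICC 0.10, falling to about 46% at an autocorrelation of 0.8.

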### Study Outcomes

We defined 2 study outcomes using EHR data, which will be examined at the clinic level and continually assessed during pre- and postimplementation periods. The first outcome, missed clinic visits, is defined as the proportion of appointments scheduled with an HIV care provider that a patient failed to attend and did not call in advance to cancel or reschedule. The second outcome, viral nonsuppression, is defined as the proportion of patients with an HIV RNA test result greater than the lower limit of detection (200 copies/mL) among those who received 1 or more HIV tests during the past 6 months.

These outcomes reflect the principle that optimal HIV care exists across a continuum, from timely diagnosis and linkage to care, to initiation of ART, and sustained adherence and retention in care over the life course [34]. They were selected because they have been identified as key quality improvement metrics by Vivent Health for all of its clinical sites. Missed visits are a marker of vulnerability for disengagement from care [35] and may predict loss of viral suppression [36] and subsequent mortality [37]. Viral suppression is the key indicator of a successful response to ART in all HIV care settings. Minimizing viral nonsuppression is, therefore, a main goal of national and global HIV elimination strategies [38].

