**HIV viral suppression outcomes**															
	HIV RNA tests completed, n	5017		4896		598		5552	2410	691		382		1147	
	Number of completed HIV RNA tests per patient, mean (SD)	3.3 (1.7)		2.7 (1.4)		3.1 (1.9)		2.2 (1.2)	2.1 (1.1)	3.4 (1.8)		4 (2)		3.2 (1.9)	
	HIV RNA tests that were nonsuppressed (%)	9.69		7.31		7.02		11.38	14.11	14.04		10.47		16.30	
	Patients with 1 or more non- suppressed HIV RNA tests (%)	21.65		16.86		13.91		27.05	30.65	26.09		15.73		37.18	

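### The power inputs mix enrolled patients, tests and all active patients, and neither the clinic-wide baseline nor the stated reach supports a fall from 26.7% to 16.7%

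*Protocol article*

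**What the plan says.** All the power inputs stand in the protocol article, Analytic Strategy: Effectiveness and Maintenance.

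- **Control rate:** "Preliminary data suggest the percentage of enrolled patients with nonsuppressed viral load (HIV RNA ≥200) before intervention to be 26.7"%. The unit is a patient and the population is those enrolled.
- **Effect:** "10 percentage point reduction in nonsuppressed HIV RNA tests in the study sites after intervention, to 16.7"%. The unit is now a test and the population is the study sites.
- **Sample and power:** "with 3682 active patients, our power to detect a 10 percentage point reduction in nonsuppressed viral loads will be 98.5"%. The population is now all active clinic patients.
- **Detectable difference:** "The study will be sufficiently powered (>80%) to detect up to a 7 percentage point reduction in patients with nonsuppressed viral load". The unit is a patient again.
- **Clustering:** "ρ=0.10, the design effect relative to an individual-based randomized controlled trial is 3.0".
- **Mechanism:** about 15% of clinic patients (631 of 4208) are reached, with a 68% improvement in suppression among them.

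Study Outcomes defines nonsuppression per patient, at clinic level, "among those who received 1 or more HIV tests during the past 6 months". Table 2 reports two clinic-wide 2-year measures, and the Results section names that table as the baseline against which later results will be compared. One measure is the percentage of "HIV RNA tests that were nonsuppressed"; the other is the percentage of patients with at least one such test.

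**The concern.** A control rate, an effect and a sample size have to describe the same unit in the same population. Here the rate is for enrollees, the effect is for tests across the sites, and the sample is everyone in active care. Because the sample is clinic-wide, the clinic-wide baseline is a fair comparator, and on neither Table 2 measure does the network start at 26.7%.

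If the planned effect is out of reach for the clinic-wide outcome, the quoted power of 98.5% describes a trial that cannot occur. A null result would then be read as strong evidence against the intervention when the trial may have had little chance of detecting what it could deliver.

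**Working it through.** **1. Reproduce the stated power.** Inputs: N = 3682 and design effect 3.0 (both stated); two equal groups and two-sided α = 0.05 (assumed, since α is not given). Effective size per group m = 3682 / 3.0 / 2 = 613.7, so √m = 24.77.

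Power = Φ{[δ√m − 1.96√(2p̄(1−p̄))] / √[p₁(1−p₁) + p₂(1−p₂)]}

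- 26.7% to 16.7%: (0.10 × 24.77 − 1.96 × 0.5829) / 0.5786 = 2.31, power **98.9%** (stated 98.5%).
- 26.7% to 19.7%: (0.07 × 24.77 − 1.96 × 0.5970) / 0.5949 = 0.95, power **82.8%** (stated above 80%).

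A Hussey–Hughes stepped-wedge calculation (8 clusters, 5 periods, ρ = 0.10, 3682/40 ≈ 92 per cluster-period) gives 98.2% to 99.0%. The arithmetic is sound.

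**2. Compare the inputs with the clinic-wide baseline (Table 2 and Results).**

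| Clinic | Tests | Tests nonsuppressed (%) | Patients with ≥1 in 2 years (%) |
|---|---|---|---|
| Milwaukee | 5017 | 9.69 | 21.65 |
| Denver | 4896 | 7.31 | 16.86 |
| Green Bay | 598 | 7.02 | 13.91 |
| St Louis | 5552 | 11.38 | 27.05 |
| Austin | 2410 | 14.11 | 30.65 |
| Kenosha | 691 | 14.04 | 26.09 |
| Madison | 382 | 10.47 | 15.73 |
| Kansas City | 1147 | 16.30 | 37.18 |

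- Per test, pooled: Σ(tests × rate) / Σ tests = 2182 / 20,693 = **10.5%**. The highest clinic is 16.30%, so all eight lie below 16.7%. A 10-point fall from 10.5% would leave about 0.5%.
- Per patient over 2 years: 1355 / 6035 = **22.45%** (Results), or 23.4% weighting the last column by clinic n. Both are below 26.7%.

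**3. Derive the clinic-wide effect from the plan's own reach.** Clinic-wide fall = reach × share nonsuppressed among those reached × improvement.

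- Share 100%: 0.15 × 1.00 × 0.68 = 10.2 points, which matches the planned 10.
- Share 26.7%: 0.15 × 0.267 × 0.68 = **2.7 points**.
- Share 35.5%: 0.15 × 0.355 × 0.68 = **3.6 points**.

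The 35.5% is 1355 / 3816, the fraction of the expected-eligible group with at least one nonsuppressed test in 2 years. The Textbox 1 criteria (medication lapse, missed appointment or substance use) do not require nonsuppression, so a share of 100% has no support. No effect is credited to the patient-directed component.

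Power with the formula in step 1, N = 3682:

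| Base rate | Fall of 2.7 points | Fall of 3.6 points |
|---|---|---|
| 26.7% | 19% | 31% |
| 22.45% | 21% | 35% |
| 10.5% | 38% | 61% |

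The 61% is a favourable pairing: the lowest base with the highest share.

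**4. Keep the planned relative reduction instead.** 10 / 26.7 = 37.5%. The 6-month per-patient rate is not given; as an assumption it may lie between about 10.5% and 22.5%.

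- From 10.5% to 6.6% (3.9 points): power **about 70%**.
- From 22.45% to 14.0% (8.4 points): power **about 97%**.

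**The case against.** The best defence is that the word for tests in the effect sentence is a slip. The 26.7% is stated per patient, 16.7% is simply 26.7% minus 10 points, and both the detectable-difference sentence and the outcome definition are per patient. On the per-patient row of Table 2, clinics run from 13.91% to 37.18%, three exceed 26.7% and six exceed 16.7%. Among patients expected to be eligible, 35.5% had a nonsuppressed test, so 26.7% is not implausible for enrollees.

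This stands in part. A reader might infer that Table 2 directly refutes the 26.7%. It does not: the per-test row contradicts the effect sentence as worded, not a rate labelled for enrolled patients. But a rate for enrollees cannot serve as the control rate for 3682 clinic-wide patients, and the network's per-patient figure is lower even with a 2-year window.

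A reader might also infer that the power is miscalculated. It reproduces, and a fixed 10-point fall from a lower base has higher nominal power (99.6% from 22.45%).

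Finally, one could put the pooled per-test rate into the reach formula (0.15 × 0.105 × 0.68 = 1.1 points, power about 9%). The documents do not support that as the plan's own scenario, because the reached patients are meant to be those at higher risk.

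**Conclusion.** The point holds as a fault in the inputs. The control rate, effect and sample size refer to different units and populations, and none is tied to the 6-month, clinic-level outcome. The clinic-wide baseline does not support a fall from 26.7% to 16.7%, and the stated reach and improvement yield 10 points only if every reached patient is nonsuppressed.

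On the plan's own reach, with 26.7% to 35.5% of reached patients nonsuppressed, the fall is about 2.7 to 3.6 points and power stays below 80% on every base examined (19% to 61%). This rests on two-sided α = 0.05, design effect 3.0, N = 3682 and no benefit from the patient-directed component; a real benefit there would raise the figures.

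The documents do not show that the control rate is near the per-test rate, since the tested-only 6-month denominator differs from both Table 2 measures. Under a constant relative reduction, power could be anywhere from about 70% to about 97% across the assumed range. The true power therefore cannot be fixed from the article; what can be said is that 98.5% is not supported.

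**What to change.** 1. From the December 2021 to November 2023 extract, tabulate the control rate by clinic exactly as Study Outcomes defines it: patients with a nonsuppressed result among those tested in a 6-month window.
2. Use that unit and the clinic-wide population for the control rate, effect, sample size and detectable difference. Keep any rate for enrolled patients separate and labelled as such.
3. Derive the clinic-wide effect from the stated reach, the stated improvement and an explicit share nonsuppressed among those reached. State separately any effect assumed for the patient-directed component.
4. Restate the power and detectable difference, with α and sidedness, over a plausible range of the control rate and that share.

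The cost is one re-tabulation of data in hand and revised wording. The outcome definition, analysis model and data collection need not change. The drawback is that the stated power will probably become less favourable.
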